# The effects of probiotic *Saccharomyces boulardii* on the mental health, quality of life, fatigue, pain, and indices of inflammation and oxidative stress in patients with multiple sclerosis: study protocol for a double-blind randomized controlled clinical trial

**DOI:** 10.1186/s13063-019-3454-9

**Published:** 2019-06-24

**Keywords:** Multiple sclerosis, Probiotics, *Saccharomyces boulardii*, Inflammation, Oxidative stress

## Abstract

**Background:**

The relationship between gut dysbiosis and inflammatory diseases including multiple sclerosis (MS) is presently recognized as an important health issue. It has been established that some bacterial probiotic strains are effective in treating MS. This study will investigate the effect of yeast probiotic *Saccharomyces boulardii* (SB) supplements on mental health, quality of life, fatigue, pain, and indices of inflammation and oxidative stress in MS patients.

**Methods/design:**

In this double-blind randomized controlled two-group parallel trial, 50 MS patients who meet the inclusion criteria will be recruited from outpatient settings. They will be randomly allocated to 4 months of daily placebo or the SB probiotic intervention. Blood samples will be taken from each participant at the baseline and after the intervention period to assess inflammation and oxidative stress. The primary endpoint will be the changes in their mental health evaluated by the 28-item General Health Questionnaire. The secondary endpoints include changes in: (1) quality of life, evaluated by the 36-item Short Form Questionnaire, (2) fatigue, evaluated by the Fatigue Severity Scale, (3) pain, evaluated by a visual analogue scale, and (4) serum levels of indices of inflammatory stress (high-sensitivity C-reactive protein) and oxidative stress (malondialdehyde and total antioxidant capacity). Moreover, any adverse events and side effects due to the intervention will be documented.

**Discussion:**

There is a need to discover safe and practical methods for managing the symptoms of MS. This trial will gather evidence on the effects of a probiotic.

**Trial registration:**

Iranian Clinical Trial Registry, IRCT20161022030424N1. Registered on 9 April 2018.

**Electronic supplementary material:**

The online version of this article (10.1186/s13063-019-3454-9) contains supplementary material, which is available to authorized users.

## Background

Multiple sclerosis (MS) is a neurodegenerative immune-mediated inflammatory disease distinguished by damage to the myelin sheaths of axons in the central nervous system [1]. MS affects at least 2.3 million people globally and is among the most frequent causes of neurological disabilities in young adults, particularly women [2].

Evidence linking diet to inflammation has emerged in recent years [3, 4]. This may be important for MS, since damage due to inflammation is the main stimulus for the neural damage seen in MS. There is an enhanced release of pro-inflammatory cytokines in MS, resulting in severe peripheral and central inflammation and leading to myelin demolition and axon destruction [5]. Previous studies have also confirmed that oxidative stress plays a fundamental role in MS pathophysiology [6, 7]. On the other hand, the gut microbiota is significantly affected by diet. Various scientific studies have attempted to evaluate the influence of gut microbiota and diet on the symptoms of MS.

In recent years, many animal and preclinical studies have established that the gut microbiota plays an important role in various aspects of human physiology, such as immunity, and it can regulate brain signals through the “microbiome–gut–brain axis” [8, 9]. Studies of experimental autoimmune encephalomyelitis, the mouse model of MS, have also shown that a disturbance to the gut microbiota affects the vulnerability to autoimmune encephalomyelitis [10, 11]. Moreover, variations in the gut microbiome of MS patients and dysbiosis have been suggested by a number of studies as possible factors [12–14].

If we accept that the gut microbiota affects the symptoms of chronic diseases such as MS, then we may be able to manage these diseases through changing the composition of the gut microbiota by adopting the right lifestyle or via probiotics. The effect of probiotic supplements in MS patients has been shown in a number of studies. Tamtaji et al. [15] showed that taking daily probiotic supplements containing *Lactobacillus acidophilus*, *L. casei*, *Bifidobacterium bifidum*, and *L. fermentum* (2 × 10^9^ colony-forming units (CFU) per g each) for 12 weeks down-regulates the expression of the messenger RNA of inflammatory markers of interleukin-8 and tumor necrosis factor alpha in mononuclear cells from the peripheral blood of MS patients. These probiotic supplements also improve Expanded Disability Status Scale scores and mental health, as measured with the Beck Depression Inventory, the 28-item General Health Questionnaire (GHQ-28), and the Depression Anxiety and Stress Scale [16]. According to Tankou et al. [17], probiotic supplements lead to an anti-inflammatory immune reaction, in the form of a reduced number of inflammatory monocytes. They may have a synergistic effect with new MS medications.

Heretofore, researchers often selected strains of bacterial species naturally present in the intestinal flora, such as lactobacilli and bifidobacteria. Thus, there is limited data on the effects of *Saccharomyces boulardii* (SB) supplements in MS patients. SB, which is a probiotic yeast, has unrivaled physiological attributes. It is stable under different pH levels, temperatures and when exposed to bile salts and gastrointestinal enzymes [18]. Numerous clinical investigations have shown that SB is better than other probiotics such as *Lactobacillus* and *Bifidobacterium* [19–22] in reestablishing the gut microbiota and aiding digestion [23, 24]. Moreover, it is resistant to antibiotics because it is a yeast [25].

On the other hand, recently published papers have recommended further studies on SB [26]. Thus, this trial will study the effects of SB supplements on mental health, quality of life, fatigue, pain, and indices of inflammation and oxidative stress.

## Method/design

### Study design

The present study is a prospective randomized double-blind placebo-controlled parallel-group clinical trial to evaluate whether probiotic SB treatment for 4 months can improve mental health, quality of life, fatigue, pain, and indices of inflammation and oxidative stress in patients with MS. The researchers and the subjects are blind to the group assignment since the probiotic supplements and the placebo are completely identical and indistinguishable from one another. Enrollment began in June 2018 (Fig. 1).

**Fig. 1 Fig1:**
[figure not shown]
Participant flow diagram

### Hypothesis

Compared with a placebo, probiotic supplements containing SB (10^10^ CFU per capsule) will improve mental health, quality of life, fatigue, pain, and serum levels of indices of inflammatory and oxidative stress in MS patients.

### Specific objective

This study aims to determine the effects of probiotic SB supplements on the mental health, quality of life, fatigue, pain, and serum levels of indices of inflammatory and oxidative stress in MS patients.

### Subjects

#### Allocation

Patients attending outpatient clinics at the Emam Reza Hospital of Tabriz University of Medical Sciences who have been diagnosed with relapsing–remitting MS will be sent information about the project, including its methods and objectives. They will then be invited to an initial assessment to determine if they meet the inclusion and exclusion criteria. The protocol and trial procedures will be described to all participants. They will have an opportunity to discuss any issues, so that they are fully informed about all trial procedures. After informed consent has been obtained by the principal investigator, the patients will be randomly assigned to receive either the probiotic supplement or the placebo for 4 months.

#### Inclusion criteria

Patients can be included if they meet all the inclusion criteria:They are aged 18–55 years.They have clinically definite relapsing–remitting MS diagnosed according to the McDonald criteria.They have an Expanded Disability Status Scale score ≥4.5.They have been referred to an outpatient clinic of the Emam Reza Hospital of Tabriz University of Medical Sciences.They are able to answer verbal questions.

#### Exclusion criteria

Patients will be excluded if they meet any of the exclusion criteria:They are in an acute or severe phase of MS.At the beginning of the study, they are undergoing an active relapse.They smoke or consume alcohol.They are pregnant.They have used antibiotics or probiotics within the past 3 months.They have used corticosteroids within the past month.They have acute gastrointestinal problems within a month before or during the trial.They have been treated with interferon within 30 days prior to study enrolment.They have taken teriflunomide, fingolimod, or dimethyl fumarate within the past 3 months, natalizumab within the past 6 months, or rituximab, cyclophosphamide, or other immunosuppressive drugs within the past year.

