#### Sample size

The main objective of this study is to determine the effect of probiotic SB supplements in comparison with a placebo on the mental health of MS patients, as evaluated by the GHQ-28. A similar study [16] found standard deviations of 6.2 and 6.4 in GHQ-28 scores for the intervention and placebo groups, respectively, and 6.5 was considered as the minimal clinically important difference. Based on a type 1 error rate (alpha) of 0.05 and a type 2 error rate (beta) of 0.10 (power = 90%) and using a two-way test, 20 participants are required in each group. Since we expect five dropouts per each group, the sample size is 25 patients per group.

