### Outcomes

#### Participant timeline

Figure 2 is the timetable of follow-up visits and measurements. It follows the SPIRIT guidelines. Each participant will visit the study center every 2 weeks. During these follow-up visits, they will receive sufficient capsules for the next 14 days. Throughout the study, participants will be contacted weekly by telephone to monitor their intake of the supplements and to prevent dropouts. If any participant discontinues with the trial, follow-up data will still be collected for them.

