### Adverse outcomes

All research staff will be asked to report any health problems related to the study at any time. All serious adverse events, whether associated or not with the intervention, will be documented on paper and electronic case report forms. All adverse events will be noted in the publication of the results.

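### An exclusion criterion that runs on into the treatment period lets randomized patients be excluded for acute gastrointestinal problems, and its meaning after randomization needs to be reconciled with the follow-up rule

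*Protocol article*

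**What the plan says.** The Exclusion criteria section of the protocol article opens with "Patients will be excluded if they meet any of the exclusion criteria" and lists, among the criteria, "They have acute gastrointestinal problems within a month before or during the trial". The other criteria describe the patient's status at entry or a look-back period. This is the only one that expressly extends into the trial.

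The Allocation section puts the eligibility check before randomization: "They will then be invited to an initial assessment to determine if they meet the inclusion and exclusion criteria". Consent follows, and then "the patients will be randomly assigned to receive either the probiotic supplement or the placebo for 4 months".

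The Participant timeline section states: "If any participant discontinues with the trial, follow-up data will still be collected for them". The Sample size section allows for losses as follows: "Since we expect five dropouts per each group, the sample size is 25 patients per group". The Statistical analysis section names a mixed effects model and no restricted analysis population.

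**The concern.** An eligibility criterion should be decidable before allocation. This one cannot be fully decided until four months of capsules have been taken, so as written a patient can be randomized, develop acute gastrointestinal problems, and then be excluded.

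The event is not neutral with respect to treatment. The Background section credits the yeast with advantages "in reestablishing the gut microbiota and aiding digestion", and the Discussion lists mechanisms in the intestinal mucosa. On the protocol's own rationale, the capsules could make such problems rarer or more frequent. The event may also be related to the primary outcome, because one of the four GHQ-28 subscales is somatic symptoms.

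Removing patients from an analysis because of a post-randomization event that treatment may affect means that the groups compared are no longer those created by randomization. Blinding does not prevent this. Such removals would also use up patients in a trial of 25 per arm.

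**Working it through.** **1. The passages side by side**

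- Allocation: criteria are checked at an initial assessment, then consent, then randomization.
- Exclusion criteria: an acute gastrointestinal problem during the trial leads to exclusion. Apart from any short gap between assessment and randomization, this can only be met by a randomized patient.
- Participant timeline: data are still collected on those who discontinue.

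After randomization, exclusion could mean stopping the capsules, leaving follow-up, or leaving the analysis. The first fits the follow-up rule and the second contradicts it. The third is not settled, because collecting data is not the same as analysing them.

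**2. The plan's own sample size**

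Inputs from the Sample size section: SDs 6.2 and 6.4, difference 6.5, alpha 0.05 ("two-way" read as two-sided), power 90%.

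- Pooled SD = √((6.2² + 6.4²)/2) = √39.7 = 6.30.
- n per group = 2 × 39.7 × (1.960 + 1.282)² / 6.5² = 19.7, rounded up to 20.
- With five dropouts, 25 per group (5/25 = 20%).

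Both stated figures reproduce. With the noncentral t distribution, power at 20 per group is 88.9%.

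**3. Shift in the estimate if cases are dropped from the analysis**

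Let p be the proportion of an arm with the event and d the number of GHQ-28 points by which cases score worse than non-cases. If m is the mean of the non-cases, the mean of all randomized patients in the arm is m + p·d, and the mean of those retained is m. Dropping cases therefore changes the between-arm difference by

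|p₁d₁ − p₂d₂|, which is d × |p₁ − p₂| when d is the same in both arms.

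The documents give neither p nor d. The values below are assumptions that show a range.

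| Event rates | d (points) | Shift (points) | Share of 6.5 |
|---|---|---|---|
| 10% vs 10% | equal in both arms | 0 | 0% |
| 5% vs 15% | 3 | 0.10 × 3 = 0.30 | 5% |
| 5% vs 15% | 6.5 | 0.10 × 6.5 = 0.65 | 10% |
| 5% vs 20% | 6.3 (1 SD) | 0.15 × 6.3 = 0.945 | 15% |
| 5% vs 25% | 6.5 | 0.20 × 6.5 = 1.30 | 20% |

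Equal rates alone do not guarantee a zero shift. With 10% in each arm but d = 6.5 in one and 3 in the other, it is 0.10 × 6.5 − 0.10 × 3 = 0.35 points. The arm with more, or worse-scoring, cases is the one that looks better once they are dropped, so the direction cannot be known in advance.

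**4. Loss of power**

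If removals came on top of the five planned dropouts per arm, two-sided t-test power for 6.5 points (SD 6.30) would be:

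| Analysed per arm | Power |
|---|---|
| 20 | 88.9% |
| 18 | 85.2% |
| 17 | 83.1% |
| 15 | 77.9% |

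**The case against.** The strongest reply is that removal from the analysis is inferred. No section says that a patient excluded during the trial leaves follow-up or the analysis. The follow-up rule can be read as the answer: capsules stopped, data kept. An article may also leave the definition of the analysis population to the full protocol or analysis plan, so its absence is not a fault. This stands, and it makes the bias conditional. It does not remove the defect, because the article does state a rule of exclusion, and that rule reaches randomized patients without saying what it does to them.

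A reader might go further and infer that the rule hides a safety signal. The documents do not support that. The Abstract says that adverse events and side effects due to the intervention will be documented. The Adverse outcomes section states "All serious adverse events, whether associated or not with the intervention, will be documented on paper and electronic case report forms" and commits to noting all adverse events in the publication. The Data monitoring section has an independent committee check adverse outcomes every month.

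A reader might also infer a definite inflation of type I error. At 20 per arm the standard error is 6.30 × √(2/20) = 1.99. A spurious shift of 0.945 points would raise two-sided rejection from 5% to about 7.5%, and a shift of 0.30 points to about 5.2%. This requires that the true difference among all randomized patients is zero. If gastrointestinal events themselves worsen GHQ-28 and nothing else differs, the 0.945 points are a real difference. Dropping the cases would then mask it, with rejection staying near 5%. The documents do not show which mechanism would apply.

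The assumed rates also have no support in the documents. The tolerability reports cited in the Discussion are favourable, and 20% of 25 is five patients, exactly the planned dropout allowance, so losses beyond it are only a possibility. Finally, the words at issue may be the article's only statement of a treatment-stopping rule, so simply deleting them could remove something the sponsor intended.

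**Conclusion.** The concern holds in a conditional form. An event that can occur after randomization, and that the product may influence, has been placed among the eligibility criteria. This does not fit the pre-randomization eligibility check, and it sits badly with the promise to follow those who discontinue.

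The comparison is at risk of bias only if affected patients are dropped from the analysis and event rates or types of patient differ by arm. Under those assumptions the shift runs from zero to roughly 1 point (1.3 at the most unequal rates tried), against a target of 6.5, in either direction. The power cost depends on losses exceeding the planned five per arm, and is about 6 percentage points for three more (88.9% − 83.1% = 5.8). The documents do not show that bias will occur or that safety information will be lost. This is a wording defect worth correcting while enrollment is open; it is not a demonstrated failure of the design.

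**What to change.** Reconcile the Allocation, Exclusion criteria and Participant timeline sections:

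- Limit the gastrointestinal eligibility criterion to the period before randomization.
- State that a randomized patient who develops an acute gastrointestinal problem remains in follow-up, is analysed in the assigned group, and has the event reported by arm.
- State separately what, if anything, the event means for taking the capsules. That is a clinical matter for the sponsor and is not judged here; the amendment should not remove a stopping rule by accident.
- If anyone has already been excluded under the present wording, collect their outcome data where possible and include them.

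The cost is a short amendment of a few sentences. It needs no extra patients or visits, because fortnightly visits and follow-up of those who discontinue are already planned. The Trial status section says that enrollment is ongoing, so an early change limits any loss of data that could not be recovered later.

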#### Sample size

The main objective of this study is to determine the effect of probiotic SB supplements in comparison with a placebo on the mental health of MS patients, as evaluated by the GHQ-28. A similar study [16] found standard deviations of 6.2 and 6.4 in GHQ-28 scores for the intervention and placebo groups, respectively, and 6.5 was considered as the minimal clinically important difference. Based on a type 1 error rate (alpha) of 0.05 and a type 2 error rate (beta) of 0.10 (power = 90%) and using a two-way test, 20 participants are required in each group. Since we expect five dropouts per each group, the sample size is 25 patients per group.

#### Randomization and blinding

Random Allocation Software [27] was used to generate block-randomized lists. Altogether, 50 eligible participants will be randomized by a trained individual. The randomization ratio will be 1:1. We will stratify the randomization based on three variables, which will be equally distributed across the two groups: (1) body mass index, (2) age, and (3) type of medication. The random number list is stored securely at the Physical Medicine and Rehabilitation Research Center. The researchers do not have access to the list. To maintain the blinding, the allocation will be kept in opaque envelopes numbered consecutively from 1 to 100. None of the participants, the treating clinicians, or the outcome assessors will be aware of the intervention group status.

#### Lifestyle guidance

Participants in both groups will be given nutritional and lifestyle recommendations by a dietitian, which emphasize: (1) increasing their consumption of fruit and vegetables, (2) decreasing their consumption of energy-dense and low-nutrient density foods and drinks, (3) potion size management, and (4) increasing physical activity.

#### Intervention group

The intervention group will take BioDigest capsules once daily for 4 months. Each capsule contains 250 mg of SB (10^10^ CFU) plus a lactose filler and a magnesium stearate lubricant. The intervention capsules will be produced and packed by Takgene Pharmaceutical Company, Tehran, Iran.

#### Control group

The control group will take placebo capsules once daily for 4 months. In terms of shape, size, taste, smell, and other exfoliation characteristics, they are quite similar to the Biodigest capsules except that they do not contain any microorganisms. The placebo capsules will also be produced and packed by Takgene Pharmaceutical Company, Tehran, Iran.

### Outcomes

#### Participant timeline

Figure 2 is the timetable of follow-up visits and measurements. It follows the SPIRIT guidelines. Each participant will visit the study center every 2 weeks. During these follow-up visits, they will receive sufficient capsules for the next 14 days. Throughout the study, participants will be contacted weekly by telephone to monitor their intake of the supplements and to prevent dropouts. If any participant discontinues with the trial, follow-up data will still be collected for them.

**Fig. 2 Fig2:**
[figure not shown]
SPIRIT schedule of enrolment, interventions, and assessments

#### Primary outcome

The primary outcome is the difference in mental health evaluated by the GHQ-28 [28] in MS patients receiving probiotic supplements and the placebo.

#### Secondary outcomes

All physicians and researchers involved in this study will attend a workshop before the first participant is recruited to ensure that the assessments and data collection are conducted properly. In this study, the following data will be collected:Checklist: This covers the inclusion criteria. It is completed at the baseline and indicates whether the patient is eligible for participation.Demographic questionnaire: This includes age, level of education, employment status, income, age of first menstrual period, etc.Mental health (Section 2.5.6)Quality of life (Section 2.5.7)Fatigue Severity Scale: This nine-item tool is used to evaluate fatigue for different chronic conditions and disorders including MS [29]. The applicability of the Persian version of the questionnaire to assess fatigue in MS patients has been established [30].Visual analogue scale: This is a simple and commonly used instrument for measuring changes in the severity of pain [31].WeightFood intake (Section 2.5.9)Physical activity (Section 2.5.5).Blood pressureBlood tests (Section 2.5.8)

